## Abstract

**Background:**

Despite the urgent need for palliative care for patients with advanced chronic obstructive pulmonary disease (COPD), it is not yet daily practice. Important factors influencing the provision of palliative care are adequate communication skills, knowing when to start palliative care and continuity of care. In the COMPASSION study, we address these factors by implementing an integrated palliative care approach for patients with COPD and their informal caregivers.

**Methods:**

An integrated palliative care intervention was developed based on existing guidelines, a literature review, and input from patient and professional organizations. To facilitate uptake of the intervention, a multifaceted implementation strategy was developed, comprising a toolbox, (communication) training, collaboration support, action planning and monitoring. Using a hybrid effectiveness-implementation type 2 design, this study aims to simultaneously evaluate the implementation process and effects on patient, informal caregiver and professional outcomes. In a cluster randomized controlled trial, eight hospital regions will be randomized to receive the integrated palliative care approach or to provide care as usual. Eligible patients are identified during hospitalization for an exacerbation using the Propal-COPD tool. The primary outcome is quality of life (FACIT-Pal) at 6 months. Secondary outcome measures include spiritual well-being, anxiety and depression, unplanned healthcare use, informal caregiver burden and healthcare professional’s self-efficacy to provide palliative care. The implementation process will be investigated by a comprehensive mixed-methods evaluation assessing the following implementation constructs: context, reach, dose delivered, dose received, fidelity, implementation level, recruitment, maintenance and acceptability. Furthermore, determinants to implementation will be investigated using the Consolidated Framework for Implementation Research.

**Discussion:**

The COMPASSION study will broaden knowledge on the effectiveness and process of palliative care integration into COPD-care. Furthermore, it will improve our understanding of which strategies may optimize the implementation of integrated palliative care.

**Trial registration:**

Netherlands Trial Register (NTR): NL7644. Registration date: April 7, 2019.

## Background

Chronic Obstructive Pulmonary Disease (COPD) is a common illness characterized by persistent respiratory symptoms and airflow limitation [1]. When the disease progresses, many patients experience recurrent acute exacerbations, often requiring hospital admissions with a mortality rate of up to 23% within 1 year after admission [2]. COPD is the third leading cause of death in the world [3]. Moreover, in advanced stages of the disease, patients suffer from multiple symptoms, which are frequently undertreated [4]. Accordingly, their health-related quality of life is comparable to, or even worse than that of patients with advanced lung cancer [5]. Thus, patients with COPD have at least a similar need for palliative care.

In line with the WHO definition, palliative care should not be restricted to reactive care in the terminal phase of the disease [6]. Instead, it should be provided proactively and earlier in the course of the disease, complementing disease-modifying care. Its goal is to enhance quality of life through assessment and treatment of physical, psychological, social and spiritual problems. Additionally, it is advocated that palliative care should take into account the maintenance of the patient’s autonomy, access to information and treatment options [7], which requires ongoing communication including advance care planning and care coordination. In accordance with current recommendations, palliative care provision should principally be provided by generalist care professionals, i.e. general practitioners and respiratory care specialists in the case of COPD-care, whereas patients can be referred to specialist palliative care if needed [7, 8]. Consequently, palliative care should be an integrated part of regular COPD-care, in which professionals collaborate in multidisciplinary teams to optimize continuity of care.

However, it is not yet clear how palliative care can be successfully integrated into COPD-care. At the moment, discussions on prognosis, goals of care and advance care planning rarely occur or only at a very late stage of the disease [9]. Neither are patients with COPD regularly referred to specialist palliative care [10]. As a consequence, patients with COPD are less likely to die at their preferred place of death, and symptoms remain undertreated [4, 11]. Previous research revealed three major barriers to palliative care provision in COPD [9, 12]. First, the unpredictable disease trajectory of COPD makes it difficult to determine when to start palliative care and discuss advance care planning. The second barrier is the lack of palliative care communication skills of professionals. The third barrier is related to a lack of care continuity and collaboration between healthcare professionals [12, 13].

In the COMPASSION (a central element in the provision of COPD-care [13] and acronym for COPD Palliative and Supportive care Implementation) study, we attempt to overcome these barriers towards the implementation of palliative care. In collaboration with patient and professional organizations, we developed an integrated palliative COPD care intervention that integrates existing scientific and practical knowledge. Moreover, to facilitate uptake of the intervention among healthcare professionals, a multifaceted implementation strategy was developed comprising a training, an online toolbox and support with planning and monitoring of implementation.

In this article, we will describe the aim, design and procedures of the COMPASSION study. Both the implementation process and clinical effectiveness of the integrated palliative care approach will be assessed. The COMPASSION study aims to:
investigate the effect of the implementation of integrated palliative care on patient, informal caregiver and healthcare professional outcomes;investigate the effect of the multifaceted implementation strategy on implementation outcomes and explore what barriers hamper the implementation of integrated palliative care in routine COPD-care;explore the relationship between implementation level and patient outcomes.

## Methods

### Design

We follow an effectiveness-implementation hybrid design type 2, as proposed by Curran et al. [14], which allows us to simultaneously test the implementation strategy and impact of the integrated palliative care intervention on health outcomes. To study effectiveness, a cluster randomized controlled trial will be performed in eight hospital regions in the Netherlands. Furthermore, the implementation process will be evaluated using mixed methods. Each hospital region will serve as a cluster. Randomization on this cluster level instead of one-to-one randomization was chosen to reduce contamination: it is likely that professionals exposed to the implementation strategy also would treat patients assigned to the control condition differently [15].

### Setting

This study will take place in eight pulmonary care departments of Dutch hospitals that collaborate with affiliated general practitioners, home care organizations and palliative care consultation teams further referred to as ‘hospital regions’. To increase comparability, academic hospitals were excluded.

### Participants

#### Healthcare professionals

Each participating hospital region forms an intervention group consisting of at least one of the following professions: pulmonologist, respiratory nurse of pulmonology care department, palliative care consultant in the hospital, general practitioner specialized in asthma and COPD, general practitioner specialized in palliative care, consultants from the regional palliative care consultation teams. The following professionals can be involved facultatively if present in that region: respiratory nurse in primary care, pulmonologists in training, practice nurse and other relevant professionals.

#### Patients

Patients diagnosed with COPD and admitted to the hospital for an acute exacerbation will be invited to participate in the study. Patients not able to complete questionnaires in Dutch, patients with severe cognitive decline (e.g. dementia) and patients on the waiting list for lung transplantation will be excluded. After completion of the baseline questionnaire, patients will be screened using the Propal-COPD tool [16]. Patients with a positive Propal-COPD score will be included in the effectiveness study. The Propal-COPD tool consists of seven indicators: Medical Research Council (MRC) dyspnea score of 5, Clinical COPD Questionnaire (CCQ) score > 3, forced expiratory volume in 1 s lower than 30% predicted, presence of specific comorbidities, body-mass index lower than 21 kg/m2 or weight loss (> 10% in the last 6 months or > 5% in last month), previous hospitalization for acute exacerbation in the last 2 years (last 2 years ≥2 admissions or last year ≥1 admission), and a negative answer to the surprise question (“Will you be surprised if your patient would die in the next coming 12 months?”) [16]. For each indicator, specific weight is given, together generating a total score. A score exceeding the previous published cut off value of − 1.362 corresponds with a high probability for death within 1 year, which is considered a proxy for having palliative care needs.

#### Informal caregivers

Informal caregivers of included patients will be invited to participate by asking the patient to indicate who gives him or her the most help and support at home.

### Recruitment of regions

To recruit hospital regions for participation, invitational letters will be sent to the heads of departments of respiratory medicine of all hospitals in the Netherlands. After agreement to take part in the study, eight hospital regions will be selected for randomization to the intervention or control group. Participating regions will be offered a small reimbursement of expenses (maximum €2.5 K per region).

### Randomization

Hospital regions will be randomly allocated by an independent statistician to the intervention or control condition, stratified by the number of COPD exacerbation hospital admissions per year.

### Blinding

To minimize response bias, patients and informal caregivers will not be told whether their hospital is assigned to the intervention or control group. Also, the researcher will be blinded during the analysis process of effect outcomes, using recoded identification numbers of participants. Blinding of professionals for cluster group allocation will not be possible due to the nature of the implementation strategy and intervention. However, professionals of control regions will be blinded for the Propal-COPD score. As a consequence, it remains unknown to them which patients take part in the effectiveness study and receive follow-up questionnaires.

### Project organization

This study is part of a national project coordinated by the Lung Alliance Netherlands, in cooperation with the Leiden University Medical Center and the Radboud University Medical Center, with financial support from The Netherlands Organization for Health Research and Development (ZonMw). A steering group for coordination and three expert groups is set up, representing the relevant patient, family and professional organizations in the Netherlands. In the development phase of the project, every 6 to 8 weeks meetings took place in which the three expert groups gave input on (i) patient-professional communication and compassionate care, (ii) identification of palliative care needs and professional’s expertise, and (iii) implementation and future dissemination, respectively. Additionally, existing practical tools and useful links were selected for an online toolbox supporting professionals.

### Intervention

Table 1 details the components of the integrated palliative care approach, consisting of an integrated palliative care intervention and an multifaceted implementation strategy. Figure 1 shows the causal assumptions of its outcomes and mechanisms of impact, based on the Medical Research Council framework [26]. The integrated palliative care intervention developed follows existing palliative care guidelines [27, 28], the Quality Framework Palliative care of the Netherlands [29], a literature review and input from the expert groups. For the identification of patients that are likely to benefit from palliative care, the previously validated Propal-COPD tool will be used. This tool has been validated in patients admitted to the hospital for acute exacerbation and showed to have a high sensitivity of 90% and specificity of 73% [16]. Moreover, admission for an acute exacerbation of COPD is considered to be one of the key milestones for transition towards a palliative approach [30] and seems to be a feasible moment to start proactive palliative care [31, 32]. After identification, one or more consultations take place either in the outpatient clinic or in the general practice, depending on the patient’s needs, for a multidimensional assessment, symptom management and advance care planning. The treatment plan and agreements made will be documented and shared with other involved professionals and discussed in a multidisciplinary meeting if needed. In case of preference for care at home, the responsibility will be transferred to the patient’s general practitioner. If a patient deceases, the provided end-of-life care will be evaluated with the patient’s informal caregiver and involved healthcare professionals.

**Table 1 Tab1:** Description of the implementation strategy and integrated palliative care intervention of the Compassion study

**Implementation strategy**		
***Components***	***Content of the component***	***Tools/materials/ underpinning theory***
Formation of regional intervention group	Multidisciplinary regional team	Implementation strategies integrated into multiple settings and directed to multiple professions involved are more effective [17]
Access to online toolbox	Website with information and guidance on the core elements of palliative care in COPD, including tools and links for facultative use	Quality Framework [7] Input from experts
Training session 1 (3 h)	Introductory information on the project and research	n.a.
	Instruction the Propal-COPD tool to identify the palliative phase in patients with COPD	Propal-COPD tool [16]
	Multidimensional assessment (physical, psychological, social, spiritual)	Adapted version of Problems Square [18]
	Communication training on advance care planning in COPD including roleplay with actors	Training in palliative care communication with roleplay supports implementation [19–21]
	Non-pharmacological and pharmacological dyspnea management	Breathing Thinking Functioning model [22]
Training session 2 (3 h)	Discussion current palliative care as organized in region vs. desired palliative care	7-phase model [23]
	Introductory information on implementing care pathway	7-phase model [23]
	Filling in formats A to E (who does what how and when) leading to first draft of regional action plan	Flowchart on patient care process (see Fig. 2)
	Assigning local implementation leaders	7-phase model [23]
Completion of regional action plan	Agreement on who does what how and when	Format regional action plan Action planning stimulates behavior change [24] and assures the suitability of the intervention to the existing structure of the region
Monitoring	Monitoring meetings on site	Audit and provide feedback to monitor, evaluate, and modify provider behavior [25]
	Evaluation meetings with local implementation groups	Share local knowledge on how implementers and clinicians made something work in their setting and then share it with other sites [25]
**Integrated palliative care intervention**		
***Components***	***Content of the component***	
Identification	Calculation of Propal-COPD score	
	Planning first consultation with patient and informal caregiver	
Multidimensional assessment	Assessing palliative care needs on physical, psychological, social and spiritual dimension	
Symptom management	Non-pharmacological and pharmacological treatment for breathlessness and other physical symptoms, smoking cessation, medication review, anxiety and depression	
Advance care planning	Education about the illness trajectory and discussions with patient and informal caregiver on goals and preferences for future medical treatment	
Coordination & continuity	Individual care plan, documentation of advance care directives	
	Information exchange and cooperation with general practitioners and other involved professionals	
	Regular multidisciplinary meetings	
Dying phase & bereavement care	Planning a consultation with informal caregiver to evaluate care in the last phase	
	Planning an evaluation of the provided palliative care with all involved professionals

**Fig. 1 Fig1:**
[figure not shown]
Medical Research Council derived model [26] illustrating causal assumptions of outcomes and mechanisms of impact. Abbreviation PC: palliative care

To facilitate the uptake of the integrated palliative care intervention, an implementation strategy was developed that consists of multiple components [17]. An online toolbox describing the core elements of integrated palliative care and providing easy access to validated, existing tools was established. Also, we developed an interactive training including roleplay for participating healthcare professionals. The training consists of two sessions of 3 h and addresses the core elements of integrated palliative care and its implementation. We collaborated with experienced training actors whose training sessions have been well received in previous research on advance care planning in dementia [33]. Also, the adapted version of the earlier developed Problems Square was used [18]. This tool is a practical translation of the WHO palliative care definition and helps professionals structuring the inventory of actual and possible future problems, and needs and wishes across multiple dimensions. Furthermore, non-pharmacological and pharmacological dyspnea management was discussed. In the second training session, each region collaboratively decides who should be involved, and which steps need to be performed by whom, how, where and when, leading to a regional action plan. In this plan, the different steps of the patient care process are elaborated (see Fig. 2). In order to guide and monitor the implementation and execution of the regional action plans, there will be regularly monitoring meetings with the project leaders of each intervention region. During the study period, every 4 months meetings with participating professionals of the intervention regions will take place in which experiences and recommendations can be exchanged.

**Fig. 2 Fig2:**
[figure not shown]
Flowchart on the care process for the individual patient

Following the recommendations of Mohr et al. [34], we will not evaluate a locked-down version of the intervention, but the implementation of the essential, core elements of the integrated palliative care intervention that will be responsible for the intervention effect. This means that healthcare professionals of all participating settings are allowed to fine-tune the intervention to organizational, professional and patient characteristics. This iterative refinement will result in continuous improvement of the intervention during the study period. Similarly, small adaptations to the online toolbox can be made based on incoming process evaluation data [34].

### Control

Healthcare professionals of the control group will provide care as usual. For the Netherlands, this means that all healthcare professionals have online access to all existing guidelines on palliative care (including dyspnea) and COPD, possibility to consult specialized palliative care teams in primary care as well as in hospitals. After the recruitment of participants has been completed, professionals of the control group will be offered similar training as the intervention group received, and they will get access to the online toolbox.

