### Procedures

After randomization and formation of a regional intervention team, participating professionals of all eight hospital regions will be sent the baseline questionnaire by email. This will be repeated 3 and 12 months after the training (intervention regions) or the inclusion of the first patient (control regions). A physician or nurse with knowledge of the study will check all COPD-patients admitted to the pulmonology care department due to an acute exacerbation, and their informal caregiver if applicable, for eligibility. After the informed consent procedure, participating patients and informal caregivers complete the questionnaires required for the Propal-COPD tool and the baseline questionnaires during the hospital stay. A physician or nurse will enter the Propal-COPD tool indicators and baseline characteristics in an online data management system. The system automatically calculates the Propal-COPD score, based on the published algorithm [16]. For a patient of the intervention region, the score will be displayed as “positive” or “negative” and in the control regions it will be displayed as “xxx”. A patient with a positive Propal-COPD score and, if present, his or her participating informal caregiver, will be sent follow-up questionnaires 3 and 6 months after inclusion. Questionnaires will be sent on paper or digitally via email, depending on personal preference. A flowchart of the cluster randomized controlled trial is shown in Fig. 3.

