### Effect evaluation

An overview of the data collection process, detailing the timing of data collection and the outcome measures and instruments used, is provided in Table 2.

**Table 2 Tab2:** Data collection schedule and measurement instruments for patients, informal caregivers and healthcare professionals

	Measurement instrument				
**Patient**		**T0**	**T3**	**T6**	**R**
Baseline characteristics	Questionnaire on demographic characteristics and case report form on disease severity	x			
Quality of life (primary outcome)	Functional Assessment of Chronic Illness Therapy-Palliative care (FACIT-Pal) scale [35]	x	x	x	
Spiritual well-being	Functional Assessment of Chronic Illness Therapy - Spiritual Well-Being (FACIT-Sp-12) scale [36]	x	x	x	
Anxiety and depression	Hospital Anxiety and Depression Scale (HADS) [37]	x	x	x	
Disease-specific health-related quality of life	Clinical COPD Questionnaire (CCQ)	x	x	x	
Satisfaction with care	Single item question on satisfaction with provided care, self-rated on a numeric rating scale (NRS) from 0 to 10	x		x	
Unplanned healthcare use	Medical record assessment on number of ED visits (without admission), hospital admission (number and number of days), ICU admission (number and number of days), in the 12 months pre-enrollment up to 12 months after enrollment				x
Date and place of death, place of care in last week of life if applicable	Medical record assessment (and contact with general practitioner if needed)				x
Dose received	Questionnaire on received core elements, based on three validated questionnaires [38–40]	x		x	
	Medical record assessment on core elements				x
Experiences and acceptability	Semi-structured interviews		x^a^		
**Informal caregiver**		**T0**	**T3**	**T6**	
Baseline characteristics	Questionnaire on demographic characteristics	x			
Caregiver burden	Caregiver Reaction Assessment (CRA) scale [41]	x	x	x	
Satisfaction with care	Single item question on satisfaction with provided care to the patient, self-rated on a NRS from 0 to 10	x		x	
Experiences and acceptability	Semi-structured interviews		x^a^		
**Health care professional**		**iT0**	**iT3**	**iT12**	
Self-efficacy	End-of-life professional caregiver survey (EPCS) [42]	x	x	x	
Role identity	Developed five-item question on role identity based on MIDI questionnaire [43]	x	x	x	
Satisfaction with care	Single item question on satisfaction with provided palliative care to patients with COPD, self-rated on a 5-point Likert scale	x	x	x	

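### Control regions may be offered the training and toolbox once recruitment ends, while late-included control patients can still be in their 6-month and 12-month follow-up

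*Protocol article*

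**What the plan says.** Four parts of the protocol article bear on this.

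- **Control.** The trigger is the end of recruitment: "After the recruitment of participants has been completed, professionals of the control group will be offered similar training as the intervention group received". Release of the toolbox depends on the same event. No other section delays this until follow-up has closed.
- **Abstract (Methods) and Procedures.** "The primary outcome is quality of life (FACIT-Pal) at 6 months". Patients with a positive Propal-COPD score "will be sent follow-up questionnaires 3 and 6 months after inclusion".
- **Effect evaluation, Table 2.** Unplanned healthcare use is taken from medical records "in the 12 months pre-enrollment up to 12 months after enrollment". Control professionals complete their last questionnaire (iT12) 12 months after the first patient is included.
- **Design and Intervention.** "Randomization on this cluster level instead of one-to-one randomization was chosen to reduce contamination", because "it is likely that professionals exposed to the implementation strategy also would treat patients assigned to the control condition differently". The intervention is not confined to the index admission: after identification, "one or more consultations take place either in the outpatient clinic or in the general practice".

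**The concern.** The trigger is tied to the last inclusion, but the outcomes are tied to time since each patient's inclusion. When the last control patient is included, that patient still has 6 months of primary follow-up and 12 months of healthcare-use follow-up to run. The care that the training promotes is delivered in consultations after discharge, so patients already enrolled could receive some of it. The Discussion adds that control regions were keen to change their practice and names smaller differences between arms as a threat, so uptake of an offer is plausible.

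Such exposure would bias the comparison towards no difference in the primary outcome and in 12-month unplanned care. The article states this trigger explicitly, so it is not a detail left to a fuller document, and an analysis plan could not prevent the exposure.

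**Working it through.** **Inputs from the article (Sample size calculation).** Difference 9 points, SD 25, two-sided alpha 0.05, power 80%, 121 per group, ICC 0.01, 10% loss, 347 in total, eight regions.

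**The plan's own figure.**
- Per group: 2 × (25 × (1.960 + 0.842) / 9)² = 121.1, against 121 stated.
- Design effect with 242/8 = 30.25 patients per region: 1 + 29.25 × 0.01 = 1.2925.
- Total: 242 × 1.2925 = 312.8, and 312.8 / 0.9 = 347.5, against 347 stated. The figure is reproduced.
- Effective number per arm, assuming equal arms: 347 × 0.9 / 2 / 1.2925 = 120.8. Standard error of the difference: 25 × √(2/120.8) = 3.217. Power at 9 points: Φ(9/3.217 − 1.96) = 79.9%.

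**Assumptions not in the article.** Accrual is uniform over R months and ends together in all control regions. Training takes place L months after recruitment ends, with full uptake. An exposed control patient gains the effect in proportion to the part of the 6-month window that is exposed.

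**Formulas** (for R of at least 6 months).
- Share of control patients with an open 6-month window: (6 − L)/R.
- Share with an open 12-month window: min(1, (12 − L)/R).
- Patients with an open 6-month window are exposed on average for (6 − L)/2 of its 6 months, so the mean exposed fraction over the control arm is (6 − L)²/(12R).
- Observed difference: 9 × (1 − (6 − L)²/(12R)). Power: Φ(difference/3.217 − 1.96).

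Example, R = 12 and L = 0: share 6/12 = 50%; exposed fraction 36/144 = 0.25; difference 9 × 0.75 = 6.75; power Φ(6.75/3.217 − 1.96) = 55.5%.

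| R (months) | L (months) | 6-month window open | 12-month window open | Observed difference | Power |
|---|---|---|---|---|---|
| 12 | 0 | 50% | 100% | 6.75 | 55.5% |
| 18 | 0 | 33% | 67% | 7.5 | 64.5% |
| 24 | 0 | 25% | 50% | 7.9 | 68.7% |
| 12 | 3 | 25% | 75% | 8.4 | 74.6% |
| 18 | 3 | 17% | 50% | 8.6 | 76.5% |
| 24 | 3 | 12.5% | 37.5% | 8.7 | 77.4% |

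**Professional survey.** Control iT12 falls 12 months after the first patient. Training after recruitment can precede it only if a region's recruitment ends less than 12 months after its first patient. At R = 18 or 24 it is not affected; at R = 12 it coincides with the end of recruitment.

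**With training after the last control T6,** the share with an open 6-month window is 0% for any R, and power returns to 79.9%.

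**The case against.** The case for the plan has real force.

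- **The wording sets an earliest time for an offer.** It fixes no date and no uptake. A reader might infer that control staff are trained the moment recruitment stops and that the arm is therefore contaminated; the text does not say so.
- **The route to enrolled patients is narrowed by masking.** In control regions the Propal-COPD result is displayed as xxx, and professionals do not know who is in the effectiveness study. Nothing says the scores are later revealed. Exposure would need a general change in care, or a new contact or readmission.
- **The package is smaller.** Control regions are promised training and the toolbox. The intervention regions also complete a regional action plan and have monitoring and four-monthly exchange meetings. Full effect from the first day is implausible.
- **Exposure is partly visible.** Received core elements are recorded by patient questionnaire at T0 and T6 and by record review, and implementation scores are compared between arms.

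All of this lowers the likely size, and the lag rows in the table show how quickly it falls. None of it closes the gap. Masking hides who is enrolled, but it does not stop trained professionals from changing care for all their COPD patients. Measuring received care shows contamination without preventing it.

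**Conclusion.** The point holds as a permitted and avoidable risk of contamination, with bias towards no difference in the primary outcome and in 12-month unplanned care. The trigger wording is certain; the extent of contamination is not. Under proportional benefit and full uptake, power falls to about 56-69% with no lag and to about 75-77% with a 3-month lag, for recruitment of 12 to 24 months. If few professionals take up the offer, or if late training does little for patients already discharged, the loss is smaller and could be negligible.

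Three stronger readings are not supported:

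- That this defeats the purpose of randomising regions. At R of 12 to 24 months, 50-75% of control patients complete the primary window unexposed, the rest are exposed for part of it, and the Design section claims only to reduce contamination.
- That no analysis could recover anything. Known training dates and the recorded core elements would allow a useful sensitivity analysis.
- That the professional outcomes are biased in any case. That depends on recruitment in a region ending before its 12-month survey.

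**What to change.** In the Control section, change the trigger so that training and toolbox access start after the last control-region patient has completed T6 and the control professionals have completed iT12. This is one sentence. Control regions wait about 6 months longer. The iT12 condition adds no further wait if at least 6 months separate a region's first and last inclusions, since the last T6 then falls at 6 + 6 = 12 months or later.

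For 12-month unplanned care there are two options:

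- Wait until the last 12-month window has closed, which makes the delay about 12 months in all.
- Record each control region's training date and add a sensitivity analysis that limits follow-up to the same calendar date, or to the same time since enrolment, in both arms.

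Follow-up should not be cut in the control arm alone and compared as simple person-time rates. If event rates vary with time since the index admission (an assumption), unequal follow-up between arms would itself introduce bias.
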